### Allocation

#### Sequence generation

Each patient, regardless of the study group allocated, will receive 3 g of prebiotic or placebo on the basis of standard adjuvant chemotherapy. Once a participant meets the enrollment conditions and signs the informed consent, they can open one envelope in the order of enrollment time. Prebiotic and placebo will be packaged in opaque bags without any graphics, and their appearance and smell are the same. A third party who has no direct involvement will stick the “A” and “B” codes on the packaging boxes.

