## Introduction

Colorectal cancer (CRC) is a common malignant tumor of the gastrointestinal tract that seriously affects the health of the digestive system. And the development of this tumor is a complex and multi-step process, from small dysplastic lesions of normal colorectal mucosa, through adenomatous polyps, to carcinoma in situ [1]. Based on location, CRC can be classified into left-sided CRC (LSCRC) and right-sided CC (RSCC). RSCC is defined as any tumor occurring in the cecum, ascending colon, hepatic flexure, or first two thirds of the transverse colon, while the LSCRC is defined as any tumor occurring in the latter one third of the transverse colon, splenic flexure, descending colon, sigmoid colon and rectum [2]. Worldwide, colorectal cancer (CRC) has become the third-ranked cancer in incidence and the second-ranked in mortality. It is estimated that 935,000 people died of CRC in 2020 according to the 2020 Global Cancer Statistics [3]. Lacking of physical activity, obesity, and diet were all independent factors related to the risk of CRC [4]. Some studies suggest that factors causing the imbalance of intestinal flora may also be significant to the carcinogenesis of CRC [5, 6]. Besides, different primary tumor locations differ in incidence, pathogenesis, clinical characteristics, survival prognosis, molecular biological characteristics, and gut microbiota [7]. Several studies have demonstrated that patients with LSCRC had a significantly better prognosis compared with those with RSCC [8–11].

Increasing evidence supports the character of intestinal flora in the pathogenesis and treatment of CRC. *Fusobacterium nucleatum* adheres, invades, and induces carcinogenic and inflammatory responses via its unique FadA adhesion to activate the growth of CRC cells [12]. Other than the direct effect of specific bacteria on partial tissues, the broader bacterial community may regulate the risk and progression of CRC via competitive rejection and other mechanisms. Gut microbiota-dependent short-chain fatty acids (SCFAs) generation fermented from dietary fiber exert protection against colorectal tumorigenesis in rodents [13].

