#### Randomization and blinding

After signing the informed consent form and complete baseline questionnaires, patients with LSCRC (*n* = 50) and RSCC (*n* = 50) will be randomly divided into prebiotic group (*n* = 25) and control group (*n* = 25) in a 1:1 allocation ratio, respectively. The random number will be generated by a computer and sealed in envelopes by an investigator who will not be involved in running the study and placed in a safe place. Before data analysis, participants and investigators will not know the contents of the bags, allocation, and study treatments.

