#### Sample size calculation

Since there is no clinical trial assessing the effect of intestinal flora on the bioavailability of chemotherapy drugs and the intervention endpoints of intestinal flora are currently unable to determine, the sample size is estimated based on the data from a previous clinical trial [22] which assessed the effects of synbiotics intervention on chemotherapy-related adverse effects (including diarrhea, appetite loss, nausea, and vomiting) for CRC patients received post-operative chemotherapy, showing that 20 volunteers per group had 90% power at an alpha level of 0.05 to detect significant differences. Combined with the above data from the clinical trial, the sample size in this study will be calculated statistically by the Power Analysis and Sample Size Software (PASS). Considering the long duration of the study (3 months) and the expected withdrawal of participants during the intervention, we plan to recruit *n* = 25 participants per group (*n* = 100 total).

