#### Data analysis

The visiting time of the participants is in accordance with the treatment course, so as to facilitate the retention of the participants. The measured data for each visit will be collected on paper and then recorded electronically on a secure, locked office computer. The paper version of the data will be locked in a bookcase. Only the investigators running in the study will have access to the final study dataset.

The obtained data will be analyzed by the SPSS software V26.0 (IBM, USA). Continuous data will be expressed as mean ± standard deviation (SD), and categorical data will be expressed as the number of cases (*n*) and percentage (%). Differences in parameter continuous variables and asymmetric variables between groups will be analyzed through independent samples *t* test and Mann-Whitney *U* test, respectively, using a paired *t* test to assess the effect of the intervention in each group. The normality of data will be assessed using the Kolmogorov-Smirnov test.

The results will be regarded as statistically significant if *p* values< 0.05.

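### Randomisation is stated as 25:25 within each tumour location, but the XOS–placebo tests carry no location term, and the envelope sentence does not say whether envelopes were kept by location

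*Protocol article*

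**What the plan says.** Under Randomization and blinding, "patients with LSCRC (*n* = 50) and RSCC (*n* = 50) will be randomly divided into prebiotic group (*n* = 25") and a control group of 25, "in a 1:1 allocation ratio, respectively". The Abstract gives the same split, and the Sample size calculation agrees with it: 25 "participants per group (*n* = 100 total"). Randomisation within location is therefore stated.

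Two sentences describe how it is carried out. Sequence generation says "Once a participant meets the enrollment conditions and signs the informed consent, they can open one envelope in the order of enrollment time". Randomization and blinding says "The random number will be generated by a computer and sealed in envelopes by an investigator who will not be involved in running the study". Neither says whether there is one envelope series or one per location.

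Data collection and sample handling lists, among the primary outcomes, gut microbiota, adverse reactions and capecitabine concentration compared between XOS and placebo in patients with CRC. For the tests, Data analysis says "Differences in parameter continuous variables and asymmetric variables between groups will be analyzed through independent samples" t test, with Mann-Whitney for asymmetric variables. No location term appears there.

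**The concern.** When a trial randomises within strata, the comparison of arms should account for those strata. Location is also unlikely to be neutral here. The Introduction says that left- and right-sided disease differ in gut microbiota, which is a primary outcome, and adds that "Several studies have demonstrated that patients with LSCRC had a significantly better prognosis compared with those with RSCC".

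Two different things can go wrong with an unadjusted pooled test, depending on how the envelopes were kept:

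- **Location-specific balanced series.** The arms are balanced on location, but the test leaves the between-location variation in its error term. It is then conservative and loses precision.
- **One shared series.** The arms can differ by chance in their share of left-sided patients, and that difference passes into the XOS–placebo contrast.

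The article does not say which applies. A location term deals with both.

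**Working it through.** **1. The stated figure.** 2 locations × 2 arms × 25 = 100, which agrees with the stated total.

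**2. How often the split is exact, by envelope arrangement.** Inputs from the article: 50 left-sided, 50 right-sided, 1:1 allocation. The arrangement is an assumption in each line.

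- One series of 50 per location, balanced 25:25: exact in both locations with probability 1, still opened in enrolment order, with nothing skipped.
- One shared series with 50 XOS and 50 placebo: the number of left-sided patients on XOS is hypergeometric (100, 50, 50). P(25:25 in both) = C(50,25)² / C(100,50) = 0.158; SD 2.5; 95% range 20 to 30; P(30:20 or worse, either way) = 0.071. Blocks on a shared list do not change this (simulated 0.157 to 0.160 for blocks of 2, 4 and 10).
- Unrestricted random numbers: binomial (50, 0.5) gives 0.112 per location and 0.112² = 0.0126 for both.

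**3. What an unadjusted pooled t test then does.** Assume 50 patients per arm, within-location SD 1, no treatment effect, and a left–right difference δ of 0.5 to 1.0 SD. The documents give no δ, so this is a range and not an estimate.

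Given the cell sizes, the true standard error of the arm difference is √(2/50) = 0.200. With a left-sided share p in an arm, the within-arm variance that the test uses is about 1 + p(1−p)δ² × 50/49. The critical value is 1.984 (98 degrees of freedom).

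*Exact 25:25, p = 0.5, no shift.*
- δ = 0.5: variance 1.064, SE inflated by √1.064 = 1.031, effective cut-off 1.984 × 1.031 = 2.05.
- δ = 1.0: variance 1.255, inflation 1.120, cut-off 2.22.
- Normal approximation: type I error 4.1% and 2.6%. Simulation (400,000 trials each): 4.3% and 2.8%.

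*30:20 split, p = 0.6 against 0.4.*
- Shift of the contrast: (0.6 − 0.4) × δ = 0.10 to 0.20 SD, which is 0.5 to 1.0 standard errors.
- Cut-offs: 1.984 × √1.061 = 2.04 and 1.984 × √1.245 = 2.21.
- Normal approximation: type I error 6.7% and 11.3%. Simulation: 7.0% and 11.8%.

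*Averaged over all splits from one shared balanced series.* Simulation (200,000 trials each): 4.9% for δ = 0.5 and 5.0% for δ = 1.0.

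**4. The same data with location in the model.** Type I error is 5.0% to 5.1% in every case in step 3 that fixes the split. With exact cells the standard error returns from 0.200 × 1.031 to 0.200 (3% smaller) for δ = 0.5, and from 0.200 × 1.120 to 0.200 (11% smaller) for δ = 1.0. At 30:20 it is 0.204, that is 0.200 / √0.96, a loss of 2% against exact balance.

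**The case against.** The strongest reply is that nothing here is a contradiction. The 25:25 division by location stands in the same Allocation section as the envelopes, and opening envelopes in enrolment order fits one series per location. Numbers of lists, block sizes and envelope handling are details that a condensed article may leave to the full protocol. All of that stands.

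A reader might go further and infer from the envelope sentence that there was one stack for the whole trial, that this could not give 25:25 in each location, and that staff had to skip envelopes or force late allocations. The documents do not support this. The single stack is not in the text, and no section describes skipping, capping or overriding. The 0.158 and 0.0126 apply only if that arrangement is assumed.

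It can also be said that the 30:20 figures are conditional on a split with about a 7% chance (that or worse) even with one shared series, that δ is assumed, and that the sentence on prognosis does not concern a trial outcome. This is fair and limits the size of the point. Nor does Data analysis say outright that the arms are pooled over location, and a comparison within one location is not affected.

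The objection does not remove the analysis point. The primary XOS–placebo comparison is described for patients with CRC as a whole, and the tests named for it do not reflect randomisation within location under either reading of the envelopes.

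**Conclusion.** The point holds as a modest improvement to the analysis plus a request for clarification. For a pooled XOS–placebo comparison of a continuous outcome, and an assumed location difference of 0.5 to 1.0 SD, the unadjusted t test runs at about 4.3% to 2.8% when cells are exactly 25:25, with a standard error 3% to 12% too large. Given a 30:20 split it runs at about 7.0% to 11.8%. Over all randomisations from one shared balanced series it keeps its 5% level, so the trial's overall error rate is not threatened. If location has no effect on an outcome, adjustment changes almost nothing. The figures are for the t test; the Mann-Whitney test was not computed.

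It is not established that the allocation failed, that it could not give the stated cells, or that any allocation was forced.

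**What to change.** In Data analysis, add: *Every comparison of XOS with placebo that pools the two tumour locations will include location (LSCRC or RSCC) as a factor, by a linear model with arm and location, or by a location-stratified rank test for skewed outcomes.* Comparisons within one location need no such term.

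As a clarification only, state under Sequence generation whether the envelopes came from location-specific series. If one shared series was used, report the cell sizes obtained and drop the statement of 25:25 within each location.

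The cost is a few sentences and one model term, with no extra patients, visits or staff. Trial status ends inclusion on 1 March 2023 and the article appeared on 12 April 2023, so new envelope sets would come too late. The analysis wording can still be settled, provided this is done before the data are unblinded.

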#### Randomization and blinding

After signing the informed consent form and complete baseline questionnaires, patients with LSCRC (*n* = 50) and RSCC (*n* = 50) will be randomly divided into prebiotic group (*n* = 25) and control group (*n* = 25) in a 1:1 allocation ratio, respectively. The random number will be generated by a computer and sealed in envelopes by an investigator who will not be involved in running the study and placed in a safe place. Before data analysis, participants and investigators will not know the contents of the bags, allocation, and study treatments.

#### Allocation concealment

As it is a randomized controlled study, the patients are blinded. The unblinding occurs if a patient decides to leave the protocol prematurely.

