**Methods:**

This is a double-blinded, randomized, parallel controlled clinical trial. Participants with left-sided CRC (LSCRC, *n* = 50) and right-sided CC (RSCC, *n* = 50) will randomly allocated to prebiotic group (*n* = 25) or control group (*n* = 25) and will receive either a daily XOS (3 g/day) or placebo, respectively, for 12 weeks. The primary outcomes will be the differences in the mucosa microbiota composition at different tumor locations and differences in gut microbiota composition, adverse effects, and blood concentration of capecitabine posttreatment. The secondary outcomes will include other blood indicators, short-chain fatty acids (SCFAs) concentration, quality of life, and mental health.

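### Two box codes combined with unblinding of any patient who leaves can break the blind for patients still in the trial, and contradict the promise of blinding until data analysis

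*Protocol article*

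**What the plan says.** All statements are in the protocol article.

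- Abstract, Methods: "This is a double-blinded, randomized, parallel controlled clinical trial".
- Sequence generation: "A third party who has no direct involvement will stick the “A” and “B” codes on the packaging boxes". No participant-specific number and no separate key for left-sided and right-sided tumors is described.
- Randomization and blinding: "Before data analysis, participants and investigators will not know the contents of the bags, allocation, and study treatments".
- Allocation concealment: after a sentence saying that the patients are blinded, "The unblinding occurs if a patient decides to leave the protocol prematurely". No medical need is required, and nothing limits who receives the information.
- Sample size calculation: the step from 20 to 25 per group is justified partly by "the expected withdrawal of participants during the intervention".
- Interventions: a box is handed over at each chemotherapy visit, every 3 weeks, and returned packages are counted. The labels are therefore seen repeatedly.
- Adverse effects: symptoms are asked about and graded in the office before each chemotherapy treatment. Adverse effects are one of the primary outcomes.

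**The concern.** The blinding rule and the withdrawal rule cannot both hold once a patient chooses to leave. The first keeps allocation unknown until data analysis; the second discloses it during the trial.

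The labelling scheme makes the conflict more serious. With participant-specific codes, a disclosure would concern one person. With two codes shared across the trial, the same disclosure can identify every other box.

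What is at stake is mainly the grading of symptoms such as nausea and peripheral neuropathy, which depends on what staff ask and how they judge the answer. A rater who knows the treatment can shift these grades without intending to, and adverse effects carry one of the trial's main claims.

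**Working it through.** **1. The plan's own figures.** Two tumor locations × 2 arms × 25 = 100, which matches "we plan to recruit *n* = 25 participants per group (*n* = 100 total". The withdrawal allowance follows from 25 = 20/(1 − d), so d = 1 − 20/25 = 0.20. The article states no rate. If the aim is to keep 20 per group, 20% is the most that the allowance covers.

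**2. What that 20% includes.** The Drop out criteria list violation of the chemotherapy regimen, use of antibiotics, probiotics or other prebiotics, inconsistent intake, and complications possibly due to the prebiotic. None of these has to be a patient's own decision to leave, which is the only trigger for unblinding. So 20% is an upper bound for the trigger, and its true rate must be assumed.

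**3. What one disclosure reveals.** Two codes and two treatments allow 2 possible keys. One known pair of code and treatment leaves 1. The number of patients whose allocation is then fixed, counting the leaver, is:

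- one A/B key for the whole trial, as the text reads: 100 of 100;
- separate A/B keys by tumor location (not described): 50 of 100;
- participant-specific codes: 1 of 100.

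For patients not yet enrolled, the key is known in advance, but their allocation is known only when they receive a labelled box.

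**4. Chance of at least one patient-decided withdrawal among 100.** P = 1 − (1 − d)^100, with a common rate d and independent decisions; the expected number is 100 × d.

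- d = 1% (assumed): 1 − 0.99^100 = 0.634; 1 expected.
- d = 2% (assumed): 1 − 0.98^100 = 0.867; 2 expected.
- d = 5% (assumed): 1 − 0.95^100 = 0.994; 5 expected.
- d = 20% (upper bound): 1 − 0.80^100 > 0.9999; 20 expected.

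This is the chance that the rule is triggered at some point. It does not say when, because entry is staggered and patients may leave at any time in the 12 weeks. It is also not the chance that staff learn the key, which depends on who is told.

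**5. Which outcomes are exposed.**

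- Symptoms elicited and graded by staff: exposed as soon as staff know the key.
- QLQ-C30 and HADS: questionnaires completed by participants, so exposed only if continuing participants also learn the key.
- Microbiota composition, capecitabine concentration, blood counts and liver function: laboratory measures, little affected.

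**The case against.** The strongest reply is that the withdrawal rule does not say who is unblinded. It follows a sentence about patients, so it may mean that only the leaver is told. Staff would then learn nothing unless the leaver told them. This stands as a limit on the consequence: loss of the blind for everyone is conditional, not certain. It does not remove the contradiction, because a leaver told in this way is a participant who knows the allocation before data analysis. If only the uninvolved third party were meant, the damage would be limited, but the text does not say so.

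A second reply is that an article condenses, and kit details may exist elsewhere. That would matter if the point were an omission. Here a stated rule conflicts with another stated rule.

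Several stronger readings are tempting but not supported:

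- *The first withdrawal necessarily reveals all 100 allocations and every later assessment is unblinded.* This needs the information to reach someone who sees the labels, and one key across both locations. Even then, self-completed and laboratory outcomes are not unblinded by what staff know.
- *The 20% allowance is the rate of the trigger.* It covers withdrawal from all causes.
- *Later envelopes carry A or B.* The codes are on the boxes; the envelopes are described as sealed and holding the random number.
- *Tests and taxa are chosen with the codes open.* The wording on data analysis does not say when, in relation to those choices, the codes are opened.

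**Conclusion.** The point holds in conditional form. The withdrawal rule contradicts the promise of blinding until data analysis and the double-blind claim. Under the two-code scheme as described, it can expose the allocation of up to 100 patients.

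The size rests on three assumptions: the treatment of a leaver reaches someone who sees the box codes; A and B mean the same in both tumor locations (otherwise 50 patients are exposed); and patient-decided withdrawal occurs independently at an assumed 1% to 5%, which gives a 63% to 99% chance that the rule is triggered at least once.

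The outcome at real risk is staff-elicited symptom grading, which is one part of one primary outcome. It still needs correction, because the conflict is in the stated rules and the remedy is inexpensive.

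**What to change.** - Reconcile the Randomization and blinding section with the Allocation concealment section by removing routine unblinding on withdrawal.
- Replace A and B with participant-specific box codes, linked to a list held by the uninvolved third party, so that any code-break reveals one participant only.
- State who may learn the result of a code-break, and log who learned what and when.
- For participants already treated under the A/B scheme, document every unblinding that occurred, including its date and who was informed, and report the subjective adverse-effect results in that light.

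The cost is new labels, protocol wording and a log; no extra patients are needed. Relabelling comes late: according to Trial status, inclusion was to end on 1 March 2023, before the article appeared on 12 April 2023. It can help only patients who still have boxes to receive. The wording change, the log and the reporting can be done at any stage.

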#### Auditing

The audit process will be done independently from investigators and the sponsor.

#### Sample size calculation

Since there is no clinical trial assessing the effect of intestinal flora on the bioavailability of chemotherapy drugs and the intervention endpoints of intestinal flora are currently unable to determine, the sample size is estimated based on the data from a previous clinical trial [22] which assessed the effects of synbiotics intervention on chemotherapy-related adverse effects (including diarrhea, appetite loss, nausea, and vomiting) for CRC patients received post-operative chemotherapy, showing that 20 volunteers per group had 90% power at an alpha level of 0.05 to detect significant differences. Combined with the above data from the clinical trial, the sample size in this study will be calculated statistically by the Power Analysis and Sample Size Software (PASS). Considering the long duration of the study (3 months) and the expected withdrawal of participants during the intervention, we plan to recruit *n* = 25 participants per group (*n* = 100 total).

